### Analysis

#### Sample size and power calculations

The sample size is based on the number of participants needed to provide adequate power to test the primary hypothesis, that is, to detect the hypothesized group differences in the primary outcomes. Based on our own clinical experience and estimates from other clinical trials in uncontrolled hypertensive patients
[4-6,11,63] we estimate that the cross-sectional standard deviations (SD) of SBP and DBP at baseline will be about 15/12 mm Hg. Conservatively, assuming (a) that the SD at follow-up will be 25% larger in the MINT group, (b) that the correlation between baseline and follow-up BPs will be 0.6 in the CRC patient navigation group and 0.4 in the MINT group (both due to heterogeneity of treatment response), and (c) that there are no barbershop effects (as this is an individual level intervention) on the change in BP, 200 participants per group will provide 86% power to detect a 5 mmHg differential change in SBP and the same power to detect a 4 mmHg differential change in DBP, based on testing the Time X Group interaction in a MANOVA, allowing for heterogeneous variances and serial correlations
[64]. Regarding the CRC navigation arm, a sample size of 127 participants per group is needed to provide 90% power to detect a group difference in the rate of completed CRC screening at six months from a baseline rate of 35%
[26,27,32,65] to a desired level of 60%. Consequently, we will recruit 240 participants per intervention group (allowing for 20% attrition), which will provide sufficient power to detect the hypothesized difference in both arms of the study. Power analyses were conducted using the R statistical language
[64,66].

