#### Randomization

Following the determination of eligibility, consent procedures, and completion of baseline self-report and psychosocial measures, individual-level randomization will occur via a randomization table generated by the study statistician. Participants will be randomized in 1:1 ratio to either the MINT lifestyle intervention or the CRC patient navigation intervention.

Participants will be informed of the results of randomization by an RA at the time of the baseline interview. At this time, the RA will discuss the MINT or the PN intervention/counseling session schedule, and answer any additional questions. Given the nature of the intervention, it is impossible to blind the RAs to the assigned condition. However, the dimension that the RA’s knowledge of the assigned condition could possibly affect is the BP measurement - one of the primary outcomes of this study. To reduce the potential for this bias, we will use an automated BP device (Vital Signs Monitor 300 Series; Welch Allyn; Skaneateles Falls, NY, USA). The other primary outcome, receipt of colon cancer screening, cannot be influenced by the RA’s knowledge of the assigned condition.

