#### Colon cancer screening

Logistic-type regression will be used to test the hypothesis that those assigned to patient navigation intervention will have significantly higher CRC screening rates compared to those randomized to the lifestyle intervention at six months. Clustered sampling effects due to site and physician will be incorporated using a multilevel modeling approach.

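### The 127 per group stated for CRC screening does not follow from 35% versus 60% at 90% power, so one of the printed figures is wrong or an input is unstated

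*Protocol article*

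**What the plan says.** CRC screening at six months is one of two primary outcomes. Its sample size is justified in one sentence of the section on sample size and power calculations, which says that "a sample size of 127 participants per group is needed to provide 90% power to detect a group difference". The lower of the two screening rates is 35%, which the article calls the baseline rate. The higher is introduced with the words "to a desired level of 60" per cent. That sentence gives no alpha, sidedness, test, continuity correction or design effect.

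The same section sizes the trial on blood pressure, where "200 participants per group will provide 86% power to detect a 5 mmHg differential change in SBP", and concludes that "we will recruit 240 participants per intervention group (allowing for 20% attrition"). The Randomization section specifies individual allocation in equal numbers: "Participants will be randomized in 1:1 ratio to either the MINT lifestyle intervention or the CRC patient navigation intervention". For the CRC analysis the article adds that "Clustered sampling effects due to site and physician will be incorporated using a multilevel modeling approach". The assumption of no barbershop effects in the sample size section is made only for the change in blood pressure.

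**The concern.** The sentence prints both rates, the power and the resulting number, so it can be checked as it stands. The number is about half as large again as those rates and that power require.

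This is the only place where the hypothesized effect on CRC screening is quantified, and the section relies on it to claim sufficient power for both hypotheses. If the inputs and the number disagree, a reader cannot tell what effect the trial was planned to detect. A result of about 20 points, for example, could be read as meeting the planned effect or as falling short of it.

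The wording adds to the uncertainty by calling the 35% a baseline rate. The eligibility criteria require every man to be in need of CRC screening at entry, so the 35% can only be a rate expected at six months in the arm without navigation.

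**Working it through.** **Step 1: which alpha?** None is stated, so I tested two-sided 5% against the blood pressure calculation, whose inputs are printed: SD 15 mmHg, follow-up SD 25% larger in MINT (18.75), correlations 0.6 (PN) and 0.4 (MINT), 200 per group, difference 5 mmHg.

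- Variance of change, PN: 15² + 15² − 2(0.6)(15)(15) = 180.
- Variance of change, MINT: 15² + 18.75² − 2(0.4)(15)(18.75) = 351.6.
- Standard error: √[(180 + 351.6)/200] = 1.630, and 5/1.630 = 3.067.
- Power: Φ(3.067 − 1.960) = 86.6%, against the stated 86%.

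Diastolic pressure (SD 12, difference 4) gives the same value. Two-sided 2.5% would give 79.5% and two-sided 1% would give 68.8%. Two-sided 5% is therefore the natural assumption for the CRC sentence too.

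**Step 2: try to reproduce the 127.** Inputs: p₁ = 0.35, p₂ = 0.60, difference 0.25, mean 0.475, equal groups, 90% power, z-values 1.960 and 1.2816.

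- Pooled variance: n = [1.960√(2 × 0.475 × 0.525) + 1.2816√(0.35 × 0.65 + 0.60 × 0.40)]² / 0.25² = (1.3842 + 0.8762)² / 0.0625 = 81.8.
- With continuity correction: (n/4)[1 + √(1 + 4/(n × 0.25))]² = 89.6.
- Unpooled variance: (1.960 + 1.2816)² × 0.4675 / 0.0625 = 78.6.
- Arcsine: 82.1.

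Rounded up, these are 79 to 90 per group. Fisher's exact test needs about 88 to 92. None is near 127.

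**Step 3: power at 127.** (0.25√127 − 1.3842)/√0.4675 = 2.096, so the power is 98.2%, not 90%.

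**Step 4: what would give about 127?**

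| Explanation | Result |
|---|---|
| 35% vs 55%, 90% power | 127.9 pooled, 124.8 unpooled, 128.2 arcsine; power at 127 is 89.8% |
| 40% vs 60%, 90% power | 126.1 unpooled (rounds up to 127), 129.3 pooled |
| 35% vs 60% with clustering inflation | 127/81.8 = 1.55, or 127/89.6 = 1.42 |
| 35% vs 60%, 95% power, divided by 0.8 for attrition | 101/0.8 = 126.25, rounds up to 127 |
| 35% vs 60%, two-sided 1%, continuity correction | 125 |

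For scale, take the 103 sites in the Trial status section with 444 to 480 men, which is 4.3 to 4.7 men per site. Under the form 1 + (m − 1) × ICC, inflation of 1.42 to 1.55 corresponds to an intraclass correlation of about 0.11 to 0.17. Attrition alone at 90% power does not explain the figure: 82/0.8 rounds up to 103, and 90/0.8 to 113.

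**Step 5: consequence for the trial.** Recruiting 240 per group and losing 20% leaves 192. Ignoring clustering, the CRC power is then 99.9% for 35% vs 60%, 97.8% for 35% vs 55% and 97.7% for 40% vs 60%. From a control rate of 35%, 90% power is available for a difference of about 16 points.

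**The case against.** The best defence is that 127 may be correct and the sentence merely incomplete. The CRC analysis is planned with site and physician effects, the assumption of no barbershop effects is confined to blood pressure, and a journal article may omit an inflation factor that the full protocol contains. This stands as a possibility, and it rules out simply striking the 127. It does not rescue the sentence as printed, which presents 127 as the number needed for two given rates and a given power and names no other input.

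A reader might infer that the planners meant 55% rather than 60%, because 35% versus 55% comes so close. The document does not support that reading over others. A control rate of 40% with 60% kept fits equally well, and the stated power or an unprinted inflation could also be the cause. Replacing 60% by 55% outright could introduce a new error.

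A reader might also infer that the CRC comparison is underpowered. The reverse is true for the stated effect: 127 exceeds what it needs, and the trial will have more than 127 per arm.

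It is also fair to say that the result will be judged mainly on its estimate and confidence interval, so the value of the planned effect as a benchmark is modest.

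**Conclusion.** The inconsistency is real. With two-sided 5%, which is assumed but supported by the blood pressure calculation, 35% versus 60% at 90% power needs 79 to 90 per group. The stated 127 is about 55% above the pooled figure of 82 (127/82 = 1.55) and corresponds to about 98% power. Even at two-sided 1% the pooled formula gives 117, or 125 with continuity correction.

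The article does not identify which item is wrong: the number, the control rate, the target rate, the power, or an inflation left unstated. The conclusion goes no further than that the printed figures do not belong together. The power values at 192 per arm ignore clustering, for which the article gives no figure. This is a reporting error in the justification of a primary outcome and does not threaten the trial's ability to test the CRC hypothesis.

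**What to change.** Go back to the calculation that produced 127 and correct whichever item is wrong, so that the sentence can be reproduced.

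- If 35%, 60% and 90% stand and no inflation was used, the number is about 82 per group (90 with continuity correction).
- If 127 stands, correct the rates or the power, or state the design effect that yields it.
- In either case, state the alpha and sidedness, and describe the 35% as the six-month screening rate expected in the MINT arm.

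It would also help to quote the CRC power at the 192 per arm expected after attrition. The cost is one rewritten sentence. Recruitment does not change, because the 240 per group comes from the blood pressure outcome.

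### Recruiting 240 per arm does not cover 20% attrition: it leaves 192 men, not the 200 on which the 86% power rests

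*Protocol article*

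**What the plan says.** All the figures are in the protocol article under Sample size and power calculations. For blood pressure, the plan states that "200 participants per group will provide 86% power to detect a 5 mmHg differential change in SBP" and that it has "the same power to detect a 4 mmHg differential change in DBP". The calculation is described as "based on testing the Time X Group interaction in a MANOVA", with unequal variances and correlations allowed. For colorectal cancer screening the plan asks for only 127 per group, so blood pressure sets the sample size.

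The recruitment target follows: "Consequently, we will recruit 240 participants per intervention group (allowing for 20% attrition". The section concludes that this gives enough power for both hypotheses. The matching total of about 480 appears in the Abstract, Study aims and Eligibility criteria. No other section gives a different attrition rate or a different evaluable number.

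**The concern.** Attrition is the share of enrolled men who are lost, so the recruitment number is the evaluable number divided by one minus that share. The stated target instead equals the evaluable number plus 20% of itself. As a result 200 evaluable, 20% attrition and 240 recruited cannot all be true.

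The error falls on the calculation that determines the size of the trial. Under Analysis of the primary aims, the blood pressure comparison has Time (baseline, six months) as a within-person factor. In its standard form it uses only men with both measurements, so each man lost to follow-up reduces that sample directly. A reader who later sees 20% loss would conclude from the text that the planned 200 per arm and 86% power were kept, and they would not have been.

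**Working it through.** **Inputs from the sample size section**

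- Baseline SDs: "SBP and DBP at baseline will be about 15/12 mm Hg".
- Follow-up SD: "the SD at follow-up will be 25% larger in the MINT group", hence 18.75 mmHg systolic and 15 mmHg diastolic in the MINT arm.
- Baseline to follow-up correlation: "will be 0.6 in the CRC patient navigation group and 0.4 in the MINT group".
- Differences to detect: 5 mmHg systolic, 4 mmHg diastolic.
- Allocation, from Randomization: "Participants will be randomized in 1:1 ratio".

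**Assumptions, not given in the article:** a two-sided 5% test; a follow-up SD in the navigation (PN) arm equal to its baseline SD; men lost to follow-up contribute nothing to the analysis of change.

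**Step 1. Reproduce the 86%.** The variance of change is sd₀² + sd₁² − 2·r·sd₀·sd₁.

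- Systolic, PN: 225 + 225 − 2(0.6)(15)(15) = 180.
- Systolic, MINT: 225 + 351.56 − 2(0.4)(15)(18.75) = 351.56.
- Sum: 531.56. SE at 200 per arm = √(531.56/200) = 1.630.
- Power = Φ(5/1.630 − 1.96) = Φ(1.107) = 86.6%.
- Diastolic: 115.2 + 225 = 340.2; SE = √(340.2/200) = 1.304; 4/1.304 = 3.067, the same ratio as for systolic and so the same power.

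An unequal-variance t calculation gives 86.4%. The stated 86% therefore reproduces. A one-sided test would give about 92%. A 25% larger follow-up SD in both arms would give about 83%. Neither matches the plan, which supports the assumptions used here.

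**Step 2. Check the attrition allowance.**

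- Needed to keep 200 after 20% loss: 200/(1 − 0.20) = 250 per arm, 500 in total.
- Stated: 240 per arm, 480 in total. This equals 200 × 1.20.
- Left after 20% loss from 240: 240 × 0.80 = 192 per arm, 384 in total.
- Largest loss at which 240 still leaves 200: 1 − 200/240 = 16.7%.

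**Step 3. Power at 192 per arm.**

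- SE = √(531.56/192) = 1.664.
- Power = Φ(5/1.664 − 1.96) = Φ(1.045) = 85.2% (85.0% by the unequal-variance t).
- Systolic difference detectable with 86% power: (1.960 + 1.080) × SE = 4.96 mmHg at 200 and 5.06 mmHg at 192.

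| | Evaluable per arm | Power, 5/4 mmHg |
|---|---|---|
| As the plan implies | 200 | 86.6% |
| 240 recruited, 20% lost | 192 | 85.2% |

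**Step 4. Screening outcome.** 192 per arm exceeds the stated requirement of 127, and power for 35% against 60% at 192 per arm is 99.9%.

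**Step 5. What a baseline-adjusted analysis would do.** With a common slope of 0.55, the mean of 0.6 (PN) and 0.4 × 1.25 = 0.5 (MINT), the systolic residual variances are:

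- PN: 225 − 2(0.55)(135) + 0.55²(225) = 144.6.
- MINT: 351.56 − 2(0.55)(112.5) + 0.55²(225) = 295.9.

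They sum to about 440 against 531.56. At 192 per arm, SE = √(440/192) = 1.514 and power is about 91%.

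**The case against.** The strongest reply is that nothing important changes. The article attaches 86% to 200 men and claims only sufficient power for the 240; it never says outright that 200 remain after attrition. At about 85% that claim survives, and screening has ample margin. The loss of 1.4 percentage points is smaller than the uncertainty in the SDs and correlations, which the plan itself presents as estimates. The Trial status section reports 444 men already recruited, so the target is nearly reached. One could also read the 20% as a mark-up on 200.

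Most of this bears on weight, and on weight it is right: this is not a threat to the trial. It does not remove the inconsistency. The target is presented as following from the power figures with 20% attrition allowed for, and a reader will take that to mean that 200 men survive a 20% loss. The mark-up reading is probably how the number arose, but the article shows no inflation step, and a mark-up of that kind is not an allowance for 20% attrition.

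**Conclusion.** The point holds. A target of 240 per arm covers 16.7% attrition, not 20%; at 20% it leaves 192 evaluable men per arm, 4% below the 200 behind the stated power. The consequence is minor: blood pressure power of about 85% instead of about 86%, and about 0.1 mmHg more in the detectable systolic difference. The conclusion that power is sufficient for both primary outcomes is not overturned.

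The attrition arithmetic needs only the plan's own numbers and the usual meaning of attrition. The power figures rest on the assumptions listed with the inputs, under which the plan's 86% is recovered.

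**What to change.** Correct the one sentence in Sample size and power calculations, in either of two ways:

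- 240 men per arm (480 in total) allow for up to 16.7% attrition while leaving 200 evaluable per arm and 86% power; or
- 240 men per arm, with 20% attrition, leave 192 evaluable per arm and about 85% power to detect 5 mmHg systolic or 4 mmHg diastolic.

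The second keeps the planning attrition rate and is the more informative. State the significance level and sidedness in the same sentence so that the figure can be checked.

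Raising the target to 250 per arm is not worthwhile for 1.4 points of power, and adjusting for baseline would recover more than that without further enrolment. The correction does not depend on making that change. The total of 480 elsewhere in the article stays as it is. The cost is one sentence and a slightly less favourable stated figure.

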### Analysis of the primary aims

#### Blood pressure

MANOVA will be used to test the hypothesis that those assigned to MINT counseling will, on average, exhibit greater six-month decreases in SBP and DBP than those assigned to the CRC patient navigation condition. This analysis will have one within-person factor - Time (baseline vs. six-month follow-up) - and one primary between-persons factor (Treatment Group). The outcome measure in this analysis will comprise a linear combination of systolic and diastolic BP.

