### Outcome assessments

The primary outcomes will be 1) within-patient change in systolic and diastolic BP from baseline to six months and 2) CRC screening rates as determined by colonoscopy report from the primary care provider at six months. For a complete list of measures, please refer to Table 
1.

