#### CRC screening

CRC screening will be measured primarily by self-report. At six-month follow-up, participants will be asked whether they had a colonoscopy or any other screening for colorectal cancer during the course of the study. As the study will be based in the community and not directly related to any specific CRC screening program, participants who report having had CRC screening and records of it will be requested from the health center. Participants will be asked to sign a medical release form at the time of informed consent to grant permission to the research team to obtain CRC screening reports.

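### The blood pressure analysis compares unadjusted change scores, which wastes precision and leaves the estimate open to bias if drop-out depends on baseline pressure differently by arm

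*Protocol article*

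**What the plan says.** Under Outcome assessments, the protocol article defines the blood pressure endpoint as "within-patient change in systolic and diastolic BP from baseline to six months". The Blood pressure paragraph under Analysis of the primary aims names the test: "MANOVA will be used to test the hypothesis that those assigned to MINT counseling" will show the larger decreases. It then gives the structure, "This analysis will have one within-person factor - Time (baseline vs. six-month follow-up) - and one primary between-persons factor (Treatment Group"), and adds that "The outcome measure in this analysis will comprise a linear combination of systolic and diastolic BP".

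Under Sample size and power calculations, the article states that "200 participants per group will provide 86% power to detect a 5 mmHg differential change in SBP", with the same power for 4 mmHg in DBP. That power is for the Time by Group interaction in a MANOVA "allowing for heterogeneous variances and serial correlations". For losses, "we will recruit 240 participants per intervention group (allowing for 20% attrition").

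The article does not say how a man without a six-month reading enters the analysis.

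**The concern.** With only two time points, the Time by Group interaction is the between-arm difference in mean change. This is true for SBP, for DBP and for any linear combination of the two. Taking a change score fixes the coefficient of baseline at 1. The plan's own inputs imply coefficients of 0.6 (PN) and 0.5 (MINT), so the change score over-corrects for baseline.

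Two things follow. First, precision is lost, because the over-correction adds baseline noise to the contrast. Second, the contrast is protected only while the men analysed have comparable baselines in the two arms. Randomisation secures that at entry. Drop-out that depends on baseline pressure differently by arm would undo it, and part of the resulting baseline difference would then be counted as treatment effect.

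**Working it through.** **Inputs** (Sample size and power calculations): baseline SD 15 (SBP) and 12 (DBP); follow-up SD the same in PN and 25% larger in MINT (18.75 and 15); baseline to follow-up correlation 0.6 (PN) and 0.4 (MINT); target differences 5 and 4 mmHg; 200 men per arm. The significance level is not stated; two-sided 5% is assumed.

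**1. Reproduce the plan's figure.** Variance of change = SD₀² + SD₁² − 2 × r × SD₀ × SD₁.
- PN: 225 + 225 − 2(0.6)(225) = 180
- MINT: 225 + 351.56 − 2(0.4)(15)(18.75) = 351.56
- SE = √((180 + 351.56)/200) = 1.630
- Power = Φ(5/1.630 − 1.96) = 0.866, which matches the stated 86%.

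DBP gives the same value, since 4/12 = 5/15 and both SDs scale alike. The plan's power is therefore that of an unadjusted change-score comparison. With 240 × 0.8 = 192 men per arm, SE = 1.664 and power is 0.852.

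**2. Condition on baseline.** Residual variance = SD₁²(1 − r²).
- PN: 225 × 0.64 = 144
- MINT: 351.56 × 0.84 = 295.31
- Sum 439.31, against 531.56 for the change score; ratio 0.826.
- At 200 per arm: SE = √(439.31/200) = 1.482, power 0.921.
- At 192 per arm: SE = 1.513, power 0.911.

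The ratio means that about 200 × 0.826 = 165 men per arm would give the precision that the change score reaches with 200.

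**3. Exposure to baseline-dependent drop-out.** The slope of follow-up on baseline is r × SD₁/SD₀: 0.4 × 18.75/15 = 0.5 in MINT and 0.6 in PN. Expected change therefore moves with baseline by 0.5 − 1 = −0.5 (MINT) and 0.6 − 1 = −0.4 (PN) per mmHg. If the mean baseline of those who stay shifts by m(MINT) and m(PN), then

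bias = −0.5 × m(MINT) + 0.4 × m(PN).

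The simulation used two million men per arm, normal pressures, 20% loss in each arm and a true difference of −5 mmHg. Drop-out odds were multiplied by 1.65 per SD of baseline SBP where dependence applies. That odds ratio is an assumption; the article gives none. It shifts the baseline mean of those who stay by about 1.44 mmHg.

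| Drop-out depends on baseline SBP | Bias by formula | Change score | Baseline-conditional |
|---|---|---|---|
| Not at all | 0 | −5.0 | −5.0 |
| In MINT only | +0.72 | −4.3 | −4.9 to −5.0 |
| Opposite: high leave MINT, low leave PN | +0.72 + 0.58 | −3.7 | −5.0 |
| Opposite: low leave MINT, high leave PN | −0.72 − 0.58 | −6.3 | −5.0 |
| Same direction in both arms | +0.72 − 0.58 | −4.9 | −4.9 to −5.0 |

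Where the last column shows a range, the first value is a common-slope adjustment among men with both readings. The second uses arm-specific slopes and the baseline mean of all randomised men.

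**4. Where conditioning does not help.** The same odds ratio was applied to the six-month SBP instead of baseline.

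| Drop-out depends on six-month SBP | Change score | Likelihood-type, baseline-conditional |
|---|---|---|
| In MINT only | −6.2 | −6.5 |
| Opposite: high leave MINT, low leave PN | −6.8 | about −7.4 |
| Opposite: low leave MINT, high leave PN | −3.2 | −2.5 |
| Same direction in both arms | about −5.6 | about −5.6 |

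**The case against.** Four objections have force.

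**Missing data.** A reader might infer from the word MANOVA that men without a six-month reading are deleted and that the plan prescribes a complete-case analysis. Standard software does that by default, but the article does not say so. A MANOVA can follow multiple imputation, and the rule may stand in an analysis plan that is not shown. Deletion is also not the main cause of the bias: in step 3, baseline adjustment among men with both readings removes nearly all of it in the differential cases. This objection stands, and the point is limited to the absence of baseline conditioning.

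**Equal covariances.** A reader might also infer that the test assumes equal covariance matrices against the plan's own inputs. The power section describes the MANOVA as "allowing for heterogeneous variances and serial correlations", so the article does not support that reading.

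**Speculative drop-out.** Nothing in the article shows that loss depends on baseline pressure differently by arm. The six-month procedures, payment and travel cards are the same in both arms. Planned contact differs (four MINT sessions; at least two navigation sessions, with weekly calls where barriers are multiple), but that does not establish differential loss by baseline pressure. With equal dependence in both arms the bias is only about 0.14 mmHg. The bias is thus a conditional risk.

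**Unseen pressure.** If loss depends on the six-month pressure differently by arm, the baseline-conditional estimate can be further from the truth than the change score (step 4). This is correct, and it is why the fix includes a sensitivity analysis.

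The precision argument is untouched by all four, since it assumes nothing about drop-out. It can fairly be said that 86% power is adequate already. That limits the urgency, but the gain uses data that every man has already given.

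**Conclusion.** The point holds as a worthwhile improvement to a valid analysis. Without differential drop-out, the change-score contrast is unbiased in a randomised comparison.

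The firm part is precision. On the article's own SDs and correlations, with two-sided 5% assumed, baseline conditioning raises power from 0.866 to 0.921 at 200 per arm, and from 0.852 to 0.911 at 192.

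The conditional part is bias: about 0.7 to 1.3 mmHg on a 5 mmHg effect if drop-out depends on baseline SBP in MINT only or in opposite directions at the assumed odds ratio, and close to nothing otherwise. The direction depends on which arm loses which men. The simulation also assumes normal baseline pressures, although entry requires a pressure above a threshold.

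**What to change.** In the Blood pressure paragraph under Analysis of the primary aims, replace the change-score MANOVA with a baseline-conditional analysis of six-month SBP and DBP, including all randomised men by assigned arm. One suitable form is a likelihood-based repeated-measures model with a common baseline mean and an arm-specific covariance, in line with the heterogeneity assumed in the power section. The alternative is the equivalent model of six-month pressure adjusted for baseline, with arm-specific slopes centred at the baseline mean of all randomised men. Report the six-month difference between arms in mmHg.

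Add one sensitivity analysis that shifts the six-month pressure of drop-outs, by arm, over a stated range, since neither method covers loss that depends on the unseen value. If an existing analysis plan already does this, the protocol wording only needs to be brought into line.

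The cost is a change of analysis wording and a few lines of code, with no new measurements. Trial status reports recruitment still open, so the change can be fixed before six-month data are complete.
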